### Statistical plan and data analysis

Demographic and baseline characteristics of study participants will be summarized using descriptive statistics and compared between treatment groups using two-sample t test for continuous variables and Chi-square test for categorical variables.

The proportion of patients with recurrent disease at 1-year post-transplant (the primary outcome) will be compared between treatment groups using Chi-square test. Multivariate logistic regression model will be constructed to model the probability of recurrence. The model will include treatment group, center, and covariates determined by the investigators to impact recurrent and/or those that are significantly different between groups at baseline. Binary secondary outcomes (graft survival, patient survival, acute rejection, and CD19^+^ <1%) will be analyzed similarly. Survival analysis will be performed to evaluate the effect of treatment on time to FSGS recurrence. Estimated GFR, a continuous secondary outcome, will be compared between groups using two-sample t test. Multivariate linear regression analysis will be conducted to examine the effect of treatment on eGFR adjusting for covariates.

Intention-to-treat analysis will be used. Analysis will be performed using Statistical Analysis Software (version 9.3, SAS Institute Inc., Cary, NC). A two-sided p-value < 0.05 will denote statistical significance.

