A number of clinical risk factors for recurrent FSGS have been identified including prior recurrence, European ancestry, rapid progression of primary FSGS to ESKD within 3 years, mesangial hypercellularity on primary biopsy and living related donor transplant; however these findings are inconsistent among various small studies (2, 5). A recent study from Europe identified late steroid-resistant FSGS (nephrotic syndrome that becomes resistant to steroids after an initial therapeutic response) as a strong risk factor for recurrence (3). These findings have been replicated in our recent retrospective study of a North American cohort from the Pediatric Nephrology Research Consortium (N=116) that showed that the risk of recurrent FSGS was 71% in children with late steroid-resistant FSGS compared to 36% in children with initial steroid-resistant FSGS (6). Genetic risk factors for late steroid-resistant FSGS are unknown. In the same study, we identified native kidney biopsy findings that may predict risk of recurrence. Unfortunately, an individual’s risk of recurrent disease cannot be predicted accurately prior to transplant. Thus, patients with FSGS have a high risk of recurrent disease post-transplant that is difficult to predict and leads to poor outcomes.

Post-recurrence treatment with plasmapheresis or rituximab, although often utilized, is not effective in all patients. Effective therapies and prevention strategies for recurrent FSGS are lacking (7–10). The demonstration of a possible causative circulating factor by Savin et al. (11) galvanized the field to attempt plasmapheresis to remove the permeability factor as a therapy for recurrent FSGS. Thereafter, recurrent FSGS has most often been treated with plasmapheresis to remove the as yet undetermined circulating factor, which is effective in a subset of patients. The results of uncontrolled single center case reports and series suggest a benefit from plasmapheresis (12–14), although graft loss from recurrent disease remains unacceptably high. Others who do not respond to plasmapheresis have been treated with alternate agents such as rituximab, abatacept, or high dose cyclosporine with variable responses and are at risk for rapid progression to graft failure (15–17). Ideally, we need to identify strategies to prevent recurrent FSGS before it occurs, which will lead to longer kidney transplant survival and reduced health care costs.

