### Randomization and study treatment

All participants will receive one 1.5 volume plasmapheresis session with fresh frozen plasma replacement prior to kidney transplant on day 0 or -1 as is able to be scheduled. In addition, participants will be randomized 1:1 to receive rituximab 375 mg/m^2^ intravenously following plasmapheresis with appropriate premedication of acetaminophen and diphenhydramine or to no additional therapy (US FDA IND #137324). Randomization will be stratified by history of initial steroid resistance vs. late steroid-resistant nephrotic syndrome given the significantly different risks of relapse in these two groups as well as by age (age < 18 vs. ≥18 years) (3). The randomization process will be centrally administered. DNA sample will be banked for future genetic analysis.

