### Sample size

Our recent retrospective study from the Pediatric Nephrology Research Consortium demonstrated an overall recurrence rate of 43% in children with FSGS, including patients both with and without monogenic cause of disease (35.8% in patients with initial steroid-resistant FSGS vs. 70.6% in patients with late steroid-resistant FSGS) (6). Sample size estimates are based on 80% power to detect the described difference as statistically significant at a significance level of 0.05. Seventy subjects per group (140 in total) are required to detect as significant a decrease in the rate of recurrent disease from 43% in the control group to 21% in the treatment group (50% reduction). We will target enrollment of 160 patients to account for ~15% attrition or loss to follow up.

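### The primary chi-square ignores the strata used to randomise: it is valid, but slightly conservative, and gives up about 1 to 2 points of power that a stratified test would keep at no cost

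*Protocol article*

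**What the plan says.** Under Randomization and study treatment, the protocol article gives the first stratification factor and its reason: "Randomization will be stratified by history of initial steroid resistance vs. late steroid-resistant nephrotic syndrome given the significantly different risks of relapse". The second factor follows: "as well as by age (age < 18 vs. ≥18 years". The Sample size section supplies the recurrence rates for the first factor: "35.8% in patients with initial steroid-resistant FSGS vs. 70.6% in patients with late steroid-resistant FSGS".

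The Statistical plan and data analysis section then fixes the primary comparison: "The proportion of patients with recurrent disease at 1-year post-transplant (the primary outcome) will be compared between treatment groups using Chi-square test". A logistic model of recurrence comes next, with covariates chosen by judgement or by a significant baseline difference: "The model will include treatment group, center, and covariates determined by the investigators to impact recurrent and/or those that are significantly different between groups at". It names neither stratification factor. The significance rule is "A two-sided p-value < 0.05 will denote statistical significance", and the sample size statement reads "Sample size estimates are based on 80% power to detect the described difference as statistically significant at a significance level of 0.05".

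**The concern.** Stratified 1:1 allocation keeps the arms balanced on steroid-response history and age. The true variance of the difference in recurrence proportions therefore no longer contains the part due to differences between strata. The pooled chi-square still counts that part as error. Its standard error is slightly too large, it rejects less often than 5% under the null, and it loses some power.

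The logistic model does not clearly remedy this. One of its two routes for covariates is a significant difference at baseline. Stratification is designed to prevent such differences in these two factors, so that route will tend to leave them out. The other route is investigator judgement, which may bring them in but does not guarantee it.

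At stake is a small amount of power. The Discussion section itself warns that a lower recurrence rate in adults may leave the study underpowered, so power that costs no patients is worth keeping.

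**Working it through.** **Inputs from the article.** Control 43%, treated 21%, 70 per group, 1:1 allocation, two-sided 0.05 (Sample size; Randomization; Statistical plan). Stratum rates 35.8% initial and 70.6% late (Sample size). Adults 37%, children 42% (Discussion).

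**1. The plan's own figure.** For an unadjusted test with pooled variance and no continuity correction, the mean rate is (0.43 + 0.21)/2 = 0.32 and

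n = [1.96·√(2·0.32·0.68) + 0.8416·√(0.43·0.57 + 0.21·0.79)]² / 0.22² = 69.4, hence 70 per group.

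The formula power at 70 is 80.4%. The stated sample size is reproduced and matches the unadjusted chi-square.

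**2. Implied share of late steroid resistance.** (0.43 − 0.358)/(0.706 − 0.358) = 0.072/0.348 = 20.7%.

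**3. Share of outcome variance between strata.** 0.207·0.793·0.348² = 0.0199. The total is 0.43·0.57 = 0.2451. The ratio is 8.1%.

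**4. True size of the unadjusted test under balanced strata.** 2·[1 − Φ(1.96/√0.919)] = 4.1%.

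**5. Simulation.** 300,000 trials per scenario, 70 per group, balanced within strata. The overall rates were held at 43% and 21% in two ways:
- common risk ratio 0.21/0.43 = 0.488;
- common odds ratio 0.32, giving treated rates of 15.1% (initial) and 43.5% (late).

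| Steroid-resistance strata | Chi-square | CMH |
|---|---|---|
| Type I error | 4.1% | 4.9% |
| Power, common risk ratio | 81.5% | 82.7% |
| Power, common odds ratio | 82.0% | 84.0% |

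The gain is 1.2 to 2.0 points. A separate repeat gave 4.0% versus 4.9% for size, 81.4% versus 82.4% (risk ratio) and 81.9% versus 83.6% (odds ratio). On the formula of step 1, power rises from 80.4% at 70 per group to 81.5% at 72 and 82.5% at 74, so the gain is worth about 2 to 4 patients per group.

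**6. Adding age.** With four strata, an age gap of 5 points (42% − 37%) and an assumed adult share of 30-70%, size is 4.0-4.1% versus 4.9-5.0%. Power is 81.4-81.6% versus 82.7-82.9% (risk ratio) or 81.8% versus 83.9-84.0% (odds ratio). Age adds almost nothing.

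**7. Sensitivity to the late share.** If it is 30-50% (an assumption; the article implies about 21%) and the relative reduction stays as planned, the unadjusted size is 3.7-3.9% and the gain is 1.2 to 2.3 points.

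**The case against.** The strongest reply is that nothing is broken. An unadjusted chi-square after stratified randomisation is valid, errs on the safe side, matches the test used for the sample size, and still has more than 80% power under the planning assumptions. All of this stands, and it limits the point to efficiency. A reader might infer that the trial is underpowered or its type I error uncontrolled because of this choice; the figures support neither.

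The conservatism also depends on balance within strata. With no balancing within strata, the chi-square returns to about 5%. The block scheme is not shown, so 4.0-4.1% is the near-perfect-balance limit. The stratum rates come from a retrospective pediatric cohort that included monogenic disease, whereas this trial also enrols adults and excludes known monogenic disease. Both cautions stand. They affect the size of the effect, not its direction.

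Three other stronger readings are tempting and not supported:

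- **A loss of about 3 points.** This needs a late share of 40-50% with the odds ratio fixed at 0.32. At 40%, the control rate would be 0.6·35.8% + 0.4·70.6% = 49.7% and the treated rate 0.6·15.1% + 0.4·43.5% = 26.5%, a reduction of 47%; at 50% the rates are 53.2% and 29.3%, a reduction of 45%. Neither the share nor that effect is the plan's.
- **Prior graft recurrence widens the gap.** The Introduction does list it ("A number of clinical risk factors for recurrent FSGS have been identified including prior recurrence"), but it is not a randomisation stratum. It causes no conservatism of this kind, and a CMH test on the two strata would not adjust for it.
- **Nothing says which analysis decides the trial.** The plan attaches the primary outcome to the chi-square, and the sample size agrees with that test. The logistic model reads as supporting. Any further formal ranking belongs in an analysis plan that is not shown.

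It is also fair that investigators could choose steroid-response history as a covariate, since the article calls its risks significantly different. Naming the factors would settle the matter.

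**Conclusion.** The point holds as a minor efficiency improvement. The stated primary test leaves out factors that the design itself treats as prognostic. This leaves about 0.8-0.9 points of the 5% type I error unused and costs about 1 to 2 points of power at 43% versus 21% with 70 per group. Nearly all of it comes from steroid resistance.

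The size rests on three assumptions: the article's stratum rates apply to the enrolled population, the late share is near 21%, and allocation is close to balanced within strata. Confidence is high for the direction and moderate for the exact figures.

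**What to change.** Before outcome data are analysed by arm:

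- Name as the primary analysis a CMH test stratified by steroid-response history and age group, as randomised, reported with a Mantel-Haenszel risk difference and 95% CI.
- Keep the unadjusted chi-square as a sensitivity analysis.
- In the supporting logistic model, include both stratification factors by rule and do not leave them to selection by baseline significance.

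The cost is wording in the statistical section. Both factors are already needed to randomise, so no new patients or data are required, and the sample size of 70 per group can stand.

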## Introduction

Focal segmental glomerulosclerosis (FSGS) is a clinicopathologic entity that is characterized by proteinuria +/- nephrotic syndrome, focal scarring and segmental sclerosis of the kidney glomeruli on light microscopy, fusion and effacement of the podocyte foot processes and progressive chronic kidney disease. Initial biopsies of children with nephrotic syndrome may show MCD initially followed by FSGS pathology as the disease progresses. Landmark studies over the past 15 years have identified more than 50 forms of monogenic FSGS. However, over 70% of children and approximately 80% of adults do not have an identifiable genetic cause. Non-genetic, primary FSGS is most likely caused by a circulating permeability factor as evidenced by several observations (1). At this time, the identity of the permeability factor remains unknown. There is currently no effective treatment for FSGS and the majority of patients will progress to end stage kidney disease (ESKD) requiring dialysis or kidney transplantation. Unfortunately, those patients without a monogenic cause of disease are at high risk for recurrence of FSGS after kidney transplant.

The rate of recurrence following kidney transplantation in patients with FSGS ranges between 30-50% in most studies, and in a subset of patients it may be as high as 80% (2, 3). True epidemiological estimates are not clear since many studies have included patients without genetic testing or were performed prior to the widespread availability of genetic testing. Recurrence of FSGS can occur rapidly, within minutes of transplantation, and can lead to immediate onset of proteinuria and graft dysfunction. Recurrent FSGS is definitively diagnosed with a kidney biopsy. Early kidney biopsies in recurrent FSGS often demonstrate isolated extensive foot process effacement with the classic focal sclerosis appearing only after months of proteinuria. Recurrent FSGS is the single most important cause of graft failure in patients with FSGS. Patients with recurrent FSGS have significantly decreased graft survival compared to patients without recurrence and often undergo multiple kidney transplants in their lifetime (4). They may also be declined for repeated kidney transplantation if prior allografts have been lost to recurrent FSGS.

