### Study population

This study will enroll 160 children and adults age 1-65 years at the time of transplant with biopsy-proven FSGS or minimal change disease (MCD) in their native kidney biopsy. Participants with either planned living or deceased donor undergoing their first, second or third kidney transplant will be included. Patients will be excluded if they have known monogenic FSGS or a secondary cause of FSGS (parvovirus infection, HIV, etc). They will also be excluded if they have received rituximab within 1 year prior to transplant.

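### The two-sample t test named for one-year eGFR cannot take in graft loss or death without an assigned value, and it does not use the randomisation strata

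*Protocol article*

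**What the plan says.** The Secondary outcomes section of the protocol article lists eGFR at one year as the measure of graft function. Under Statistical plan and data analysis two methods are named for it. The first is unadjusted: "Estimated GFR, a continuous secondary outcome, will be compared between groups using two-sample t test". The second is a model: "Multivariate linear regression analysis will be conducted to examine the effect of treatment on eGFR adjusting for covariates". The eGFR model's covariates are not listed. For the logistic model of recurrence, the same section names treatment group, centre, and covariates that the investigators choose or that differ at baseline.

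The only population statement is "Intention-to-treat analysis will be used". Graft loss and death also have their own comparisons: "Binary secondary outcomes (graft survival, patient survival, acute rejection, and CD19^+^ <1%) will be analyzed similarly".

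Under Randomization and study treatment, allocation is stratified by steroid-resistance history (initial or late) and by age (under 18, or 18 and over). The age range is wide: "This study will enroll 160 children and adults age 1-65 years at the time of transplant".

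**The concern.** One-year graft eGFR does not exist for a patient who has died or whose graft has failed. A t test or a linear regression then has two options. Either those patients drop out, or they are given a value and the result depends on the value chosen.

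Dropping them matters because the document itself links the missing values to treatment. The Introduction states "Recurrent FSGS is the single most important cause of graft failure in patients with FSGS", and the Sample size section plans on recurrence falling from 43% to 21%. If rituximab works as hoped, controls should lose more grafts. An available-case comparison would then set selected controls, with some of their worst outcomes gone, against a less heavily selected rituximab arm. Covariate adjustment does not bring back patients without a value.

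The second issue is precision. The trial stratifies because the strata are thought to be prognostic: the Sample size section reports recurrence of 35.8% with initial and 70.6% with late steroid resistance. A plain t test makes no use of this.

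**Working it through.** **The plan's own figure.** The article gives no eGFR mean, SD, effect size or power, and no one-year graft-loss rate. Its only sample size is for the primary outcome, and that figure reproduces:

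- Inputs (Sample size; Statistical plan): 43% vs 21%, 80% power, two-sided 0.05.
- n per group = [1.960 × √(2 × 0.32 × 0.68) + 0.842 × √(0.43 × 0.57 + 0.21 × 0.79)]² / 0.22² = (1.293 + 0.540)² / 0.0484 ≈ 69.4, so 70, as stated. Power at 70 is 80.4%.

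Nothing in that calculation bears on eGFR.

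**Illustration on assumed inputs.** From the document: 70 per arm and recurrence of p = 0.43 (control) or 0.21 (rituximab). Assumed: mean eGFR 65 without recurrence, mean 50 with recurrence and a surviving graft, SD 20 within each group, and 3% graft loss without recurrence. The graft-loss rate g among recurrences is varied.

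- Functioning grafts with recurrence: a = p(1 − g)
- Functioning grafts without recurrence: b = (1 − p) × 0.97
- Mean in functioning grafts: (50a + 65b) / (a + b)
- Mean with lost grafts set to 0: 50a + 65b

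Worked case, g = 30%:

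- Control: a = 0.301, b = 0.5529. Loss is 14.6%, functioning-graft mean 59.7, zero-scored mean 51.0.
- Rituximab: a = 0.147, b = 0.7663. Loss is 8.7%, functioning-graft mean 62.6, zero-scored mean 57.2.
- Differences: 2.9 in functioning grafts and 6.2 zero-scored.

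| g | Loss, control vs rituximab | Difference, functioning grafts | Difference, lost grafts = 0 | Understatement |
|---|---|---|---|---|
| 5% | 3.9% vs 3.4% | 3.3 | 3.4 | 0.1 |
| 10% | 6.0% vs 4.5% | 3.2 | 4.0 | 0.8 |
| 20% | 10.3% vs 6.6% | 3.1 | 5.1 | 2.0 |
| 30% | 14.6% vs 8.7% | 2.9 | 6.2 | 3.3 |

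Differences are in mL/min/1.73 m2. The understatement is taken before rounding.

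The direction depends on recurrence raising graft loss. At g = 0, with the 3% loss falling only on patients without recurrence, the functioning-graft difference (3.3) exceeds the zero-scored one (2.9).

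On these inputs neither analysis has much power. It is 14.5% (functioning grafts) vs 13.5% (zero-scored) at g = 5%, and 11.5% vs 26.1% at g = 30%.

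**Does the separate graft-survival comparison cover the gap?** The g = 30% row is about 10/70 vs 6/70 losses. The pooled proportion is 16/140 = 0.114, and z = 0.0571 / √(0.1143 × 0.8857 × 2/70) = 1.06, so p is about 0.29. The losses would be visible but not conclusive.

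**The case against.** A reader might infer that the plan restricts eGFR to patients with a functioning graft and so contradicts its intention-to-treat statement. The document does not support that. No sentence limits the eGFR population, the only stated principle is intention-to-treat, and a t test can be run with an assigned value. A conflict would arise only if the test were applied to available values. Nor is the absence of a graft-loss rule an error in itself. Such rules commonly sit in a statistical analysis plan, which is not shown, and this is a condensed article.

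It would also go too far to say that the plan hides the lost grafts, since graft and patient survival are compared as outcomes of their own. Nor can one say that age is ignored altogether. The adjusted regression may include it, and because randomisation is stratified, omitting age from the t test costs precision and does not introduce bias.

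Finally, worst-rank or zero scoring is a choice of estimand. It counts events already analysed elsewhere, and the size of the problem rests wholly on assumed figures.

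All of this stands, and it limits the point to the method that the article does fix. That method is an unstratified test of means on a quantity undefined for some patients, beside a regression not tied to the randomisation factors. The separate survival comparisons soften the problem but do not remove it. With few events, a reader could see two inconclusive results that each carry part of one benefit.

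**Conclusion.** The point holds as a weakness in the stated method for a secondary outcome. The named t test can include graft losses and deaths only through an assigned value. Applied to available values, it would select on an event that treatment is expected to affect and would probably understate a benefit. The test also leaves the two stratification factors unused, and the regression does not commit to them.

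The size cannot be derived from the document. On the assumptions above, the understatement is about 0.1 to 3.3 mL/min/1.73 m2 as graft loss among recurrences goes from 5% to 30%: negligible if early loss is rare, material if it is common. The direction assumes that recurrence raises one-year graft loss, which the Introduction supports only qualitatively. The primary comparison of recurrence is not affected.

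**What to change.** 1. Replace the plain t test as the main eGFR comparison with one that adjusts for or stratifies by both randomisation factors, age group and steroid-resistance history. For the linear regression, this means naming the two as fixed covariates.
2. Add a prespecified analysis of all randomised and transplanted patients in which graft loss and death count. Either give them the worst ranks (deaths below graft losses) with a van Elteren test over the randomisation strata, or set lost grafts to 0 in the linear model, with the value for deaths stated in advance.
3. Show the functioning-graft result alongside as descriptive, with the number of patients contributing in each arm.

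This costs plan wording and no new data. The composite is harder to read than a mean difference and overlaps with the graft- and patient-survival outcomes, so the two results should be presented together. Where early loss is rare, zero scoring gains nothing and may lose a little power. Limiting the analysis to transplanted patients departs slightly from strict intention-to-treat, so anyone randomised but not transplanted should be reported by arm. Table 1 places randomisation at the infusion visit on day -1 or 0, so such patients should be few.
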